### Patients

2.2

We recruit patients of all genders, from ages 18 to 59, with a clinical diagnosis of MDD per DSM-5 criteria (Diagnostic and Statistical Manual of Mental Disorders, 5th edition) [33]. The study is conducted at the University of São Paulo, Brazil, at two of its institutions: the University Hospital (*Hospital Universitário – HU*) and the Institute of Psychiatry of the Clinics Hospital (*Instituto de Psiquiatria – IPq/HC-FMUSP*).

The inclusion criteria are: (1) a current depressive episode of at least moderate severity, with a baseline score on the HDRS-17 [30] ≥ 17; (2) absence of contraindications to tDCS (i.e. metallic plates on the head, brain devices, brain aneurysm clips, cochlear implants, cardiac pacemakers, among others); (3) 8 or more years of formal education; (4) access to a personal smartphone and internet at home; and (5) lifetime refractoriness to no more than 3 antidepressants, at optimal doses and for an appropriate duration of 6 weeks, according to a modified Antidepressant Treatment History Form (ATHF) [34].

The exclusion criteria are: (1) other psychiatric diagnoses (i.e. schizophrenia, schizoaffective disorder, bipolar disorder, obsessive-compulsive disorder, attention-deficit and hyperactivity disorder, eating disorders, personality disorders, substance use disorders), although anxiety disorders, as comorbidities, are accepted; (2) suicidal ideation or a suicide attempt within 4 weeks or less, prior to baseline; (3) previous or current psychotic symptoms, not otherwise specified; (4) depressive symptoms better explained by other clinical conditions (i.e. hypothyroidism, anemia, congestive heart failure, among others) or other psychiatric disorders; (5) severe clinical conditions, including Post-Acute Sequelae of COVID-19 [35]; (6) epilepsy and/or other neurological disorders; (7) suspected or confirmed pregnancy; (8) lactation; and (9) use of diazepam > 10 mg per day (or equivalent doses of other benzodiazepines). Regarding other medications, no antidepressant wash-out is being performed, and antidepressant medications currently in use should be in stable doses for at least 6 weeks prior to baseline.

Patient recruitment is being performed through advertisements in our group website (www.sin.org.br) and in our social media channels (Facebook: neuropsiquiatria.ipq; Instagram: neuropsiquiatria.ipq; LinkedIn: sin-ipq). We also accept clinical referrals from health professionals. Finally, the press offices of the Institute of Psychiatry and of the University of São Paulo Medical School also perform periodic announcements regarding our project, with considerable attention from traditional media.

Our screening process consists of two stages. Firstly, interested volunteers answer an online and confidential survey, available through a secure REDCap (Research Electronic Data Capture) link, in order to provide personal contact information and answer basic multiple-choice questions regarding inclusion/exclusion criteria (Supplementary Material 1), as well as the 9-item Patient Health Questionnaire (PHQ-9) [36]. Subsequently, all survey respondents who have not preliminarily indicated any exclusion criterion, and have achieved a score on the PHQ-9 ≥ 10, are invited for a 45-minute initial online interview, with a research-team psychiatrist, in order to confirm eligibility criteria, according to the Mini-International Neuropsychiatric Interview (MINI) [37]. The two-stage online screening process has proven an asset during the COVID-19 pandemic. Before attending the onsite evaluation, volunteers are screened for COVID-19 symptoms, and if COVID-19 is suspected, a PCR SARS-CoV-2 test is required before the onsite evaluation.

If patients have been considered eligible after these two stages (surveys and online interview), they are invited for an onsite visit in our research centers, for a complete psychiatric evaluation, written and informed consent, baseline assessments, and finally, randomization if enrolled. Moreover, patients will subsequently be invited to receive the two active interventions in: (1) an open-label 6-week crossover phase, if they were previously randomized to ‘double sham’ and do not achieve response at endpoint (defined as ≥ 50% reduction in HDRS-17 scores from baseline to endpoint), and (2) a maximum 6-month open-label follow-up phase if they were previously randomized to ‘double-active’ or ‘ptES-only’ and do achieve response at endpoint. Furthermore, patients who achieve response at the end of the crossover phase are also eligible for the 6-month open-label follow-up phase (Figure 1). A new psychiatric evaluation is performed prior to entering the open-label crossover and follow-up phases, to reconfirm eligibility criteria to undertake active ptES. Finally, patients who were randomized to ‘ptES-only,’ but do not achieve response, will not be eligible for open-label follow-up, as it is unlikely they would profit from a continuation.

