In the past 15 years, several trials showed that tDCS is moderately effective for MDD, suggesting that it could be a first-line intervention, especially in patients with a low-drug resistance [6,9]. However, such an approach is hampered by the limited scalability of tDCS treatment. The relative scarcity of skilled personnel and the logistical burdens and transportation costs associated with daily visits to external facilities are probably associated with its suboptimal utilization in clinical practice. In this context, recent technological advancements are progressively allowing tDCS to be performed remotely, and operated by patients themselves, therefore reducing costs and enhancing scalability. Although this approach sounds appealing, data from home-based trials are still preliminary. A recent open-label pilot study (n = 34) [16] and case series (n = 5) [17] have suggested that home-use tDCS is a feasible intervention for MDD, following necessary precautions and safety guidelines [18]. Furthermore, these studies were open-label and did not present a control arm, limiting the interpretation of their findings.

Concomitantly to these nascent advancements in the practice of home-based tDCS, growing attention has also been directed towards the combination of tDCS and neurobehavioral or psychotherapeutic interventions, aiming to engage the same brain regions of interest, and ultimately, achieve an additive or synergistic therapeutic effect [19,20]. For instance, two pilot, randomized, sham-controlled, clinical trials (RCTs), combining tDCS and cognitive-control training (CCT) for the treatment of MDD, have demonstrated positive, but preliminary results [21,22]. These studies applied a neurobehavioral intervention with tDCS and were performed at research centers.

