### Procedures

2.4

Upon trial enrollment, patients are initially registered by our research team on the study dashboard, using a personal email as identification. Patients then receive a confirmatory email and are instructed to: (1) download the trial app (in iOS or Android), (2) create their own personal app account and password, which are validated by a trial-provided security code. Randomization (1:1:1) is performed remotely through a computer random generator, using a Mersenne Twister algorithm. Subsequently, patients receive another email for confirmation of trial enrollment, thereby completing the randomization process and trial registration, with preservation of allocation concealment.

Once patients have been enrolled and randomized, their personal accounts become visible for the research team, on the study dashboard, where only the researchers can oversee adherence to, and completion of, home-based trial sessions, all the while remaining blinded. Patients are advised not to describe their app characteristics during the clinical evaluations, for this would unblind the investigators; however, reports of ptES-related adverse events are actively assessed during these online meetings. If unblinding occurs at any point during an evaluation, patients will be referred to another blinded member of the team for the remaining part of the trial. Blinding efficacy assessments for both evaluators and patients are performed at the endpoint.

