### Sample size calculation

2.7

For Psylect, we estimated a total sample size (n) of 210 randomized patients (70 patients per arm), to achieve the ability to observe statistically significant effects, with a power of 80% (1 − β = 0.8). Dropouts were assumed to increase monotonically (Weibull) and to be equally distributed between arms. We will use 4 measurements (continuous linear change from baseline, weeks 2, 4 and endpoint), between the 3 arms (time × group interaction), in the framework of linear mixed-effects models (LMM) [51,52].

For our sample size calculations, we assumed baseline depression scores and standard deviation (SD) of 25 (±5) on the HDRS-17, distributed equally between groups, based on previous works from our group [31,32,53]. Furthermore, we considered that: (1) placebo effects in the double-sham arm will impact baseline depression scores equal to 1 effect size (ES) in SD units (ES = difference in mean change divided by SD); (2) the ‘ptES-only’ arm will have the same placebo effects present in the double-sham arm (ES = 1), plus a treatment response of ES = 0.4; and, (3) the ‘double-active’ arm will have placebo effects (ES = 1) plus a larger response of ES = 0.8. Therefore, probable endpoint scores of 20, 18 and 16 were used, for ‘double-sham,’ ‘ptES-only’ and ‘double-active,’ respectively. The effect sizes were also chosen based on the results from our previous trials and considering that tDCS and online behavioral therapies have small to moderate effect sizes.

Sample size per arm was calculated based on the smallest detectable group difference (ES tDCS vs. combination = −0.4, ES placebo vs. tDCS = −0.4). Significance levels were Bonferroni corrected for 3-way pairwise comparisons (α = 0.05/3) to control family-wise error rate, while still allowing for more anti-conservative adjustment in the final analysis [54–56].

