### Statistical analysis

2.8

As we have 3 co-primary hypotheses, each co-primary hypothesis will be considered statistically significant if a two-sided p < 0.0167 (Bonferroni-corrected) is obtained. For the analysis of the coprimary outcomes, LLM will be employed, using a first order regressive covariance structure, which includes all observed variables without the need of imputing missing data. The dependent variable is score change on the HDRS-17. Independent variables are time (all observations until week 6), and group (‘double-active,’ ‘ptES-only’ and ‘double-sham’). We will test the statistical significance between the pairwise comparisons per our primary hypotheses. We will employ an intention-to-treat (ITT) approach.

For the analysis of the secondary outcomes, linear mixed-effects models will be employed analogically to the analysis for the primary outcomes. Binary outcomes (response and remission) will be modeled using mixed logistic regression at each timepoint. Improvement in other depressive domains will be evaluated using the same linear hierarchical models described.

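### The published primary HDRS-17 model holds only time and group, so it probably gives up some precision that three known baseline factors could supply

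*Protocol article*

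**What the plan says.** **Population (section 2.2, Patients).** Eligibility allows "lifetime refractoriness to no more than 3 antidepressants, at optimal doses and for an appropriate duration of 6 weeks", assessed with a modified ATHF. There is no antidepressant wash-out; current antidepressants must have been at a stable dose for at least 6 weeks. Two hospitals take part.

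**Background (section 1, Introduction).** Of tDCS, the article says that past trials found moderate effectiveness, "suggesting that it could be a first-line intervention, especially in patients with a low-drug resistance".

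**Data held.** Section 2.4 (Procedures) and Table 1 place a Defined Daily Dose medication form at baseline. Hospital is not a line in Table 1, but it is known for each patient from where the onsite visit took place.

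**Allocation (section 2.4).** "Randomization (1:1:1) is performed remotely through a computer random generator, using a Mersenne Twister algorithm". No strata, blocks or minimisation factors are named.

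**Primary model (section 2.8, Statistical analysis).** The dependent variable is HDRS-17 change. "Independent variables are time (all observations until week 6), and group". Each contrast is tested at a Bonferroni-corrected level: "each co-primary hypothesis will be considered statistically significant if a two-sided p < 0.0167 (Bonferroni-corrected) is obtained". The secondary models follow the primary one.

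**The concern.** Section 2.8 does more than stay silent on covariates: it lists the model terms, and the list has two entries. Three facts fixed before randomisation are left out: the number of failed antidepressants, antidepressant use, and hospital. All are available without new data collection.

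If these factors are related to HDRS-17 change, leaving them out keeps explainable variation in the residual and widens the standard errors. The trial is sized on differences of 0.4 SD (2 HDRS-17 points at SD 5) at a two-sided level of 0.0167, so precision matters. Naming covariates before unblinding also rules out a choice made later, once any imbalance between arms has been seen.

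**Working it through.** **Inputs from the article.** 70 per arm; two-sided α = 0.05/3 = 0.0167; power 80%; smallest effect 0.4 SD; SD 5. Not given: the within-patient correlation, the dropout rate, and the share of variance (R²) that the three factors explain.

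**1. The plan's own figure.** The assumed endpoint means follow from the stated effect sizes: 25 − 5 × (1, 1.4, 1.8) = 20, 18, 16. For a plain comparison of two means:

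n per arm = 2 × [(2.394 + 0.842)/0.4]² = 130.9, so 131.

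At 70 per arm that comparison has 48.9% power by the normal formula (47.9% by the noncentral t). The article, however, sizes a mixed model with 4 measurements. Under compound symmetry with correlation 0.70, no dropout and free group intercepts, 70 per arm gives 79.6%. With 15% dropout and equal baselines it gives 80.8%. With AR(1), adjacent-visit correlation of 0.90 gives 79.4% (no dropout, free intercepts). These correlations and the dropout rate are assumptions. The 70 per arm can be neither confirmed nor refuted, so I take the stated 80% as the starting point.

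**2. Gain from adjustment.** At 80% power the expected z statistic is 2.394 + 0.842 = 3.236. If the covariates remove a share R² of the residual variance, the standard error is multiplied by √(1 − R²), and

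power = Φ[3.236/√(1 − R²) − 2.394].

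| R² (assumed) | SE ratio | Power | n per arm for 80% |
|---|---|---|---|
| 0 | 1.000 | 80.0% | 70 |
| 0.01 | 0.995 | 80.5% | 70 |
| 0.02 | 0.990 | 80.9% | 69 |
| 0.05 | 0.975 | 82.3% | 67 |
| 0.10 | 0.949 | 84.5% | 63 |

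The last column is 70 × (1 − R²), rounded up.

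**3. What such an R² would require.** A binary factor present in half the patients that shifts HDRS-17 change by g points adds variance 0.25 × g². Against 5² = 25, shifts of 1, 2 and 3 points give R² of 0.01, 0.04 and 0.09. The article's SD of 5 is for baseline scores. If the mixed model really reaches 80% with 70 per arm, the effective variance is smaller, 25 × 70/130.9 = 13.4, and a 2-point shift would then be 1/13.4 = 0.075. Both values lie inside the table. The shifts themselves are assumptions.

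**4. Chance imbalance.** For a factor at 50% prevalence and 70 per arm, the SD of the difference between two arms is √(2 × 0.25/70) = 0.0845. For any one contrast:

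P(difference ≥ 15 points) = 2 × [1 − Φ(0.15/0.0845)] = about 7.6%.

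If the factor shifts HDRS-17 change by 2 points, a 15-point imbalance moves that contrast by 0.15 × 2 = 0.3 points. The simple standard error is 5 × √(2/70) = 0.85 points, so this is about a third of one standard error. Against the standard error that 80% power implies, 2/3.236 = 0.62, it is about half of one. The unadjusted standard error already includes this variation.

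**The case against.** The strongest reply is that nothing in the plan is invalid. Under randomisation, an unadjusted model gives unbiased contrasts with correct type I error, and adding covariates is an efficiency option. Strata and a full covariate list are also details that an article may leave to the full protocol. The first part stands and limits the point to precision. The second holds for allocation: the article names no strata, but the full scheme is not shown, so absence of stratification cannot be asserted. It holds less well for the model, because section 2.8 lists the terms itself.

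Three stronger readings are tempting, and the article does not support them.

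- A reader might infer from the Introduction that response depends on drug resistance. The sentence is a tentative remark about where tDCS might fit in treatment. Read strictly, it points to effect modification, which would need a treatment interaction and is not addressed by covariate adjustment. The cap of 3 failed antidepressants also narrows the range of this factor. Nothing in the article says that antidepressant use or hospital predicts HDRS-17 change.
- A reader might infer that chance imbalance biases the contrasts. It does not: step 4 shows that its effect is a fraction of a standard error that already allows for it. The probability that the largest of the three pairwise imbalances reaches 15 points is about 18%, but that figure does not describe any one contrast.
- A reader might infer that the trial starts from about 48% power. That is a figure for two simple means, not for the planned mixed model with 4 measurements.

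**Conclusion.** The point holds as a modest improvement to a stated model. As published, the primary model uses none of three baseline factors that the trial already holds, and some precision is probably given up. From the stated 80%, the gain is about 0.5 percentage points of power at R² = 0.01, 2.3 at 0.05 and 4.5 at 0.10. These figures rest on an assumed R² and on taking the 80% as given; the article allows neither to be checked. If the factors are weakly prognostic, the gain is close to nil. The validity of the three co-primary tests is not in question. Adjustment for baseline HDRS-17 is a separate matter and is not counted here.

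**What to change.** Before unblinding, state in section 2.8 that the primary HDRS-17 model includes as fixed covariates the number of failed antidepressants (0 to 3, from the modified ATHF), antidepressant use at baseline (yes/no, from the medication form) and hospital. If the test is the time-by-group effect, add each covariate's interaction with time; a main effect alone does not remove variation in the slopes. Use the same covariates in the analogous secondary models. If the full protocol stratifies allocation, include those strata too.

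The cost is a short addition to the analysis section and a few degrees of freedom, with no new data. The downside is little return if the factors prove weakly prognostic.

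Leave the allocation method unchanged for the remaining patients. About 80 had started by December 2021, the full scheme is not shown, and altering it mid-trial is not warranted by a point about precision.

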### Interventions

2.3

For the combined ptES and iBT, we use tDCS devices and the iBT app developed by Flow Neuroscience™ (Malmö, Sweden) (Figure 2).

The Flow™ ptES device consists of a one-size-fits-all rechargeable headset, with circular electrodes (area = 22.9cm^2^). The anode is placed over the left prefrontal cortex, and the cathode, over the right prefrontal cortex. The device is manufactured with customized, saline pre-humidified and non-reusable sponge pads, which can be easily adjusted over the electrodes, with the aid of circular rubber bands. Flow™ ptES devices are paired, via Bluetooth, to an iBT app (Flow Depression™ – iOS/Android) and provide augmented-reality resources: when patients capture their faces on the smartphone camera, a virtual reality headset is displayed where the actual headset is to be positioned. For PSYLECT, the iBT app has been renamed and the original manufacturer contact information has been replaced with that of our research center.

Flow™ has been approved by health regulatory agencies, for home-use in adult patients with MDD, in the European Union, the United Kingdom, and Brazil (National Agency of Sanitary Health, ANVISA). Moreover, the device has undergone an electric-field (EF) simulation study [38], with 15 brain models obtained from structural MRI from previous clinical trials performed by our team, and displayed compatible EF distributions as compared to those observed in traditional tDCS montages used in those previous studies [31,32]. Furthermore, the Flow device and app have been evaluated in a previous, open-label pilot phase with 5 depressed patients, at our research center, displaying favorable tolerability, safety, and efficacy profiles [17].

For the active tDCS sessions, current strength is delivered at 2 mA (current density = 0.087 mA/cm^2^), for 30 minutes, daily for 5 continuous days (with a subsequent 2-day pause), during the first 3 weeks, and twice-weekly for the following 3 weeks (comprising a total of 21 sessions in 6 weeks). For the sham tDCS sessions, the protocol is similar, but consists of fade-in and fade-out phases of 1 mA, for 45 seconds, at the beginning and at the end of the sessions, with a silent period in between for the remaining 28.5 minutes.

The iBT intervention is performed concomitantly to the tDCS session and consists of an app-based interactive protocol (with a chatbot and online videos), synchronized via Bluetooth, to the tDCS device. For PSYLECT, the chatbot iBT protocol has been translated from English to Portuguese, and all iBT videos are either presented with Portuguese subtitles, or in the case of meditation videos (which allow patients to close their eyes), have been dubbed to Portuguese. Further details about active and sham iBT sessions are not described in this design paper to avoid breaking the blinding of future patients enrolled in this study, with means of access to this publication. The complete details will be provided when the study results are published or upon reasonable request.

### Procedures

2.4

Upon trial enrollment, patients are initially registered by our research team on the study dashboard, using a personal email as identification. Patients then receive a confirmatory email and are instructed to: (1) download the trial app (in iOS or Android), (2) create their own personal app account and password, which are validated by a trial-provided security code. Randomization (1:1:1) is performed remotely through a computer random generator, using a Mersenne Twister algorithm. Subsequently, patients receive another email for confirmation of trial enrollment, thereby completing the randomization process and trial registration, with preservation of allocation concealment.

Once patients have been enrolled and randomized, their personal accounts become visible for the research team, on the study dashboard, where only the researchers can oversee adherence to, and completion of, home-based trial sessions, all the while remaining blinded. Patients are advised not to describe their app characteristics during the clinical evaluations, for this would unblind the investigators; however, reports of ptES-related adverse events are actively assessed during these online meetings. If unblinding occurs at any point during an evaluation, patients will be referred to another blinded member of the team for the remaining part of the trial. Blinding efficacy assessments for both evaluators and patients are performed at the endpoint.

For the evaluation of depression and anxiety symptoms, we use the following scales: (1) Hamilton Depression Rating Scale, 17-item version (HDRS-17) [30], (2) Montgomery–Åsberg Depression Rating Scale (MADRS) [39], (3) Beck Depression Inventory – II (BDI-II) [40], (4) Positive and Negative Affect Scale (PANAS) [41], (5) State-Trait Anxiety Inventory (STAI) [42], and (6) Hamilton Anxiety Rating Scale (HAM-A) [43]. To evaluate for treatment-emergent manic or hypomanic symptoms and tDCS-related adverse events, the Young Mania Rating Scale (YMRS) [44] and the tDCS adverse events survey [12] are applied, respectively. Our standard tDCS adverse events questionnaire has been previously used and validated in two of our former, completed randomized clinical trials with tDCS in depression [31,32], and covers all common side effects related to tDCS, which are mainly local in nature (i.e. tingling, redness and itching at the application site). Furthermore, the questionnaire also investigates more serious adverse events such as headaches, nausea, and dizziness. All adverse events are graded from mild to severe. Furthermore, at the bottom of this tDCS questionnaire, we provide an open field where participants can freely describe any other adverse events not otherwise captured by the questionnaire, on a weekly basis. We will report all additional adverse events not otherwise captured by the structured tDCS-related adverse events questionnaire, as well as dropout rates in each arm.

Clinical usability of the device is evaluated through a 5-item Likert scale, designed specifically for this trial (which incorporates questions about the ptES device and iBT app) (Supplementary Material 2). The Edinburgh Handedness Inventory – Short Form [45], the Defined Daily Dose (DDD) medication form [46], and sociodemographic and head measurements (head circumference, nasion-inion and tragus-tragus distances) are collected at baseline. The Clinical Global Impression Rating (CGI) form is applied at baseline and endpoint [47] (Table 1).

The first ptES session of each patient is performed at our research centers, with direct supervision of unblinded members of our team, who are not directly involved with clinical evaluations. These members need to be unblinded once they offer consultations regarding app usage. In this initial training session, the different parts of the equipment are presented to the patients, as well as recommendations on when to interrupt the session (i.e. presence of pain or any serious discomfort). If any difficulties are detected during the initial training session, additional onsite training sessions can be scheduled. Once patients are deemed trained for ptES, all further sessions are performed without supervision at the patients’ homes, with recommendations to remain at physical rest (sitting or lying down), throughout the session, in a calm environment and concentrated on the app′s instructions. The app offers a tutorial on how to correctly place the headset, before each individual session, and informs patients to remove the headset after session completion. The app also notifies patients when the headset needs recharging, and sets off reminders for subsequent sessions, which can be performed after a minimum interval of 24 hours. Missed sessions can be rescheduled for the upcoming weeks, with no more than 5 sessions per week.

Patients are evaluated online on a weekly basis by the blinded members of the research staff. Moreover, all trial patients have remote access to supervision upon request by unblinded members of the team. For this purpose, we provide a mobile number for immediate contact. If medical attention is deemed necessary, due to an intercurrence or significant adverse event, an online medical appointment is performed within at most 48 hours. If needed, patients can also be referred to an onsite clinical evaluation at our research centers. Furthermore, adherence and completion of sessions are monitored online, through the study dashboard. Early unblinding and trial discontinuation before study completion are initiated by the following circumstances: (1) significant depression worsening, defined as a > 25% increase in HDRS-17 scores from baseline, during two consecutive weekly assessments; (2) development of suicidal ideation or suicide attempt; (3) development of psychotic symptoms; (4) development of (hypo) mania and/or clinically significant mixed symptoms (YMRS ≥ 8); (5) low adherence to study protocol, defined as < 75% of completed sessions, at any point during the study; (6) absence at any weekly evaluation without justification; and (7) patient consent withdrawal.

After trial completion, the endpoint assessments will be completed by blinded members of our research team. As a final step, patients and clinical evaluators will be unblinded using the study dashboard, and eligibility for the crossover and follow-up stages will be assessed. If participation in the study is terminated at the endpoint assessment, patients are referred to their original treatment facilities.

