Our secondary hypotheses are that: (1) changes in depression scores will be larger in ‘double-active’ compared to ‘ptES-only,’ in ‘double-active’ compared to ‘double-sham,’ and ‘ptES-only’ compared to ‘double-sham’ arms, using additional depression-rating scales (please refer to these scales below, in item 2.4 Procedures); (2) response (defined as ≥ 50% reduction in HDRS-17) and remission (defined as HDRS-17 ≤ 7) will be larger in ‘double active’ versus ‘ptES-only,’ ‘double-active’ versus ‘double-sham,’ and ‘ptES-only’ versus ‘double sham’ arms; (3) reduction in comorbid anxiety scores will be greater in ‘double-active’ compared ‘ptES-only,’ ‘double-active’ compared to ‘double-sham,’ and ‘ptES-only’ compared to ‘double-sham’; (4) the clinical usability of the ‘double active’ protocol will be regarded as (very) easy by ≥ 80% of recipients, according to a Likert scale specifically created for this original study; (5) all three protocols will be equally safe and tolerable, according to the tDCS Adverse Events Survey, as was observed in two large RCTs involving tDCS for the treatment of MDD, previously completed by this research team [12,31,32].

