**Figure 2 F2:**
[figure not shown]
Flow™ device designed for home use. The figure on the left shows the device and supporting iBT app. The figure on the right shows a simulation model of the electrode placement and corresponding electric field distribution on the cortex. The anode and cathode are placed over the left and right prefrontal cortices, respectively. The correct position, in terms of angulation and distance to the eyebrows, is achieved using the app<apos;>s augmented reality feature and the smartphone<apos;>s front camera.

**Table 1 T1:** Clinical scales and questionnaires used during PSYLECT.

	Baseline	W1	W2	W3	W4	W5	W6
Sociodemographic data/head measurements	✓						
Edinburgh Handedness Inventory (short version)	✓						
DDD	✓						
HDRS-17	✓		✓	✓	✓		✓
HAM-A	✓			✓			✓
MADRS	✓		✓	✓	✓		✓
CGI	✓			✓			✓
YMRS	✓		✓	✓	✓		✓
Blinding assessment - evaluator							✓
Blinding assessment - patient							✓
PANAS	✓			✓			✓
STAI-T	✓			✓			✓
STAI-S	✓			✓			✓
BDI - II	✓			✓			✓
Likert usability scale		✓	✓	✓	✓	✓	✓
tDCS side effect questionnaire		✓	✓	✓	✓	✓	✓

Abbreviations: DDD: Defined Daily Dose; HDRS-17: Hamilton Depression Rating Scale, 17-item version; HAM-A: Hamilton Anxiety Rating Scale; MADRS: Montgomery-Åsberg Depression Rating Scale; CGI: Clinical Global Impression; YMRS: Young Mania Rating Scale; PANAS: Positive and Negative Affect Rating Scale; STAI-T/STAI: State-Trait Anxiety Inventory; BDI-II: Beck Depression Inventory – II; tDCS: transcranial direct current stimulation.

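### The tDCS side effect questionnaire has no pre-treatment record, so new headache, nausea or dizziness cannot be told from existing symptoms except by attribution after the fact

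*Protocol article*

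**What the plan says.** Section 2.4 (Procedures) names two safety instruments in one sentence, the YMRS and the adverse events survey: "To evaluate for treatment-emergent manic or hypomanic symptoms and tDCS-related adverse events". It describes the effects covered as mainly local to the application site, and then adds that "the questionnaire also investigates more serious adverse events such as headaches, nausea, and dizziness". On recording, it says "All adverse events are graded from mild to severe" and provides a weekly open field. It mentions no onset date, no relatedness item and no comparison with the state before treatment.

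In Table 1 the row "tDCS side effect questionnaire" is ticked at weeks 1 to 6 and blank at baseline. The YMRS and every repeated symptom scale (HDRS-17, HAM-A, MADRS, CGI, PANAS, STAI-T, STAI-S, BDI-II) have a baseline tick. The only other repeated form without one is the usability scale, which rates use of the device and needs none.

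Section 2.1 (Overview) makes the survey the yardstick of secondary hypothesis 5: "all three protocols will be equally safe and tolerable, according to the tDCS Adverse Events Survey". No margin is stated.

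**The concern.** Headache, nausea and dizziness can exist before any current is applied. Patients enter with at least moderate depression, comorbid anxiety disorders are accepted, and for those on antidepressants "no antidepressant wash-out is being performed". The first session is held onsite after randomisation, so even the week 1 form follows stimulation.

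Without an earlier form, a symptom carried into the trial and one that began or worsened under stimulation can look the same. Any carried-in symptoms that are reported are added to all arms alike. This dilutes the contrast between active and sham stimulation. Since hypothesis 5 predicts equality and has no margin, a diluted contrast favours the trial's own prediction. An analysis plan written later can define a treatment-emergent event, but it cannot recover a form that was never collected.

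**Working it through.** **No figure of the plan to reproduce.** The article gives no adverse-event rate, safety margin, safety alpha or safety power.

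**Inputs from the article**
- Sample size: "210 randomized patients (70 patients per arm", allocated 1:1:1.
- About 80 patients had started by December 2021 (section 2.1), so at most 210 − 80 = 130 could still complete a baseline form.

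**Assumptions, not in the article**
- Emergent rates p: 10% on sham, 25% on active ptES.
- Background share b, reported in full: 10%, 20% or 30%, equal across arms and independent of emergent symptoms.
- Two-sided alpha 0.05, with the two active-ptES arms combined (70 vs 140).

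**Step 1: dilution.** Observed rate = b + (1−b)p in each arm, so observed difference = (1−b)(p_active − p_sham). At b = 30%:
- sham: 0.30 + 0.70 × 0.10 = 37.0%
- active: 0.30 + 0.70 × 0.25 = 47.5%
- difference: 10.5 points instead of 15; risk ratio 1.28 instead of 2.50.

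**Step 2: power with all reports, 210 patients.** Unpooled normal approximation: power = Φ(d/SE − 1.96). At b = 30%, SE = √(0.37×0.63/70 + 0.475×0.525/140) = 0.0715, so power = Φ(0.105/0.0715 − 1.96) = 31%.

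**Step 3: power with new symptoms only, 130 patients (about 43 vs 87).** At b = 30%:
- Denominator restricted to those free of the symptom at entry (0.7×43 = 30.1 and 0.7×87 = 60.9): SE = √(0.09/30.1 + 0.1875/60.9) = 0.0779, power = Φ(0.15/0.0779 − 1.96) = 49%.
- Denominator of all 130 (7.0% vs 17.5%): SE = √(0.0651/43 + 0.1444/87) = 0.0563, power = Φ(0.105/0.0563 − 1.96) = 46%.

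| Background b | Observed rates, sham vs active | Difference (points) | Power, all reports, 210 | Power, new only, 130 |
|---|---|---|---|---|
| 10% | 19.0% vs 32.5% | 13.5 | 59% | 58–59% |
| 20% | 28.0% vs 40.0% | 12.0 | 42% | 52–54% |
| 30% | 37.0% vs 47.5% | 10.5 | 31% | 46–49% |

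**Step 4: sensitivity to the test.** With a pooled-variance test, power = Φ((d − 1.96·SE0)/SE). For the first case in step 3, the pooled rate is (30.1×0.10 + 60.9×0.25)/91 = 0.200 and SE0 = √(0.200×0.800×(1/30.1 + 1/60.9)) = 0.0892. Power is then Φ((0.15 − 1.96×0.0892)/0.0779) = 38%. The same formula gives, for new only against all reports, 35–38% against 30% at b = 30%, 41–43% against 40% at b = 20%, and 47–48% against 54% at b = 10%. The gain is smaller on this test, and at 10% background there is a loss.

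**Step 5: single active arm against sham, 70 vs 70, pooled test.** Power with all reports falls from 65% (b = 0) to 45%, 32% and 24% at b = 10%, 20% and 30%. The direction does not depend on combining the active arms.

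**The case against.** **The article does not say that pre-existing complaints will be counted as events.** A reader might infer from the blank baseline cell that every one of them will be. The text does not support that. Section 2.4 describes the target as events related to tDCS or ptES, assessed in weekly meetings, and the instrument is cited rather than reproduced, so an attribution item cannot be excluded. This stands, and the point is limited to the missing pre-treatment record. Attribution recalled after stimulation is a weaker basis than such a record.

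**The effects covered are mainly local.** This stands too. Tingling, redness and itching under the electrodes hardly need a baseline. Only the non-specific items are at issue.

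**Background symptoms may be few.** Not every patient takes an antidepressant, and neurological disorders, severe clinical conditions and higher benzodiazepine doses are excluded. The article gives no rate, so this can be neither confirmed nor dismissed.

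**The sham arm already deals with it.** In part. Randomisation prevents a false difference between arms, but it does not undo the (1−b) shrinkage. That a missed difference favours hypothesis 5 also owes something to the absent margin, which a baseline form does not cure.

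**The counting rule can be left to the full protocol or analysis plan.** True of the definition, but not of the data collection, which Table 1 fixes.

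**Conclusion.** The point holds in limited form. For headache, nausea and dizziness, the schedule leaves no pre-treatment record, and the comparison for hypothesis 5 is pulled toward no difference by a factor (1−b) to the extent that existing symptoms are reported. The direction follows from the arithmetic, given background symptoms that are balanced across arms and independent of emergent ones. The size is unknown because the article gives neither background nor emergent rates.

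It would be too much to conclude that a baseline form roughly doubles power. The assumed rates give 66–69% against 31% at a 30% background only if all 210 patients had the form. With about 130, the gain is moderate at 30%, smaller at 20% and absent at 10%, and on a pooled test it is smaller still. This is a cheap improvement to a secondary outcome. It does not affect the efficacy comparisons.

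**What to change.** For patients still to be enrolled, tick the Baseline column of Table 1 for the same questionnaire, completed at the onsite visit before the first session. Analyse the non-specific items as symptoms that are new or of higher grade than at baseline, and present this next to the analysis of all reports in all 210 patients. Leave the local effects as they are.

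The cost is one short existing form at a visit that already takes place, plus a one-line definition. The downside is that 80 or more earlier patients lack the form. The refined analysis therefore covers at most about 130, later-enrolled patients, and the report must carry two event definitions, clearly labelled. Keeping the all-reports analysis guards against the case where background symptoms are rare and the smaller subset brings no gain.
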